#### Interim analyses {21b}

No interim analyses are planned.

#### Methods for additional analyses (e.g. subgroup analyses) {20b}

Additionally, subgroup analyses are planned for the three primary cluster C PDs (avoidant, dependent, obsessive–compulsive) and the otherwise specified PD with predominantly cluster C traits.

#### Methods in analysis to handle protocol non-adherence and any statistical methods to handle missing data {20c}

An intention-to-treat analysis will be performed for the primary outcome measure. Missing data will be reduced to a minimum by using suitable measures described above.

#### Plans to give access to the full protocol, participant level-data and statistical code {31c}

On request and with the agreement of the research group, the full protocol can be made available by the corresponding author. The data on participant level will not be shared with external parties or on external repositories, because of privacy issues, sensitivity of the data and the policies for data security.

## Oversight and monitoring

### Composition of the coordinating centre and trial steering committee {5d}

This study is designed, performed and coordinated at Arkin/NPI. Daily support for the trial is carried out by as follows:Principal investigator: takes supervision of the trial and medical responsibility of the patients.Data manager: organizes data capture, safeguards quality and data.Study coordinator: trial registration, coordinates the study, annual safety reports.Research assistant: identifies potential recruits, takes informed consent, conducts interviews and ensures follow-up according to protocol.

The research committee meets biweekly. There is no trial steering committee or stakeholder and public involvement group. Contact with the client advice board from Arkin is established.

### Composition of the data monitoring committee, its role and reporting structure {21a}

A DSMB has not been assigned for this study in accordance with the ethical committee of the VU Amsterdam.

### Adverse event reporting and harms {22}

For participants of this study, no direct risks are expected or foreseen. Any adverse events reported by the patient or observed by the investigator, other members of the research team or therapists will be documented. An adverse event is defined as an undesirable experience that happens to a participant during the study, whether or not related to the experimental intervention.

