**Methods:**

In this mono-centre pragmatic randomized clinical trial, 290 patients with Cluster-C PDs or other specified PD with predominantly Cluster-C traits, will be randomized to one of three treatment conditions: group schema therapy for Cluster-C (GST-C, 1 year), schema-focused group therapy (SFGT, 1.5 year) or psychodynamic group therapy (PG, 2 years). Randomization will be pre-stratified on the type of PD. Change in severity of PD (APD-IV) over 24 months will be the primary outcome measure. Secondary outcome measures are personality functioning, psychiatric symptoms and quality of life. Potential predictors and mediators are selected and measured repeatedly. Also, a cost-effectiveness study will be performed, primarily based on a societal perspective, using both clinical effects and quality-adjusted life years. The time-points of assessment are at baseline, start of treatment and after 1, 3, 6, 9, 12, 18, 24 and 36 months.

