### Objectives {7}

The aim of this pragmatic randomized clinical trial is to compare the effectiveness and cost-effectiveness of three group therapy formats that are regularly delivered in clinical practice to patients with a Cluster-C PD in a superiority study design. The primary outcome is the severity of the Cluster C-PD. The slopes over time of the three treatments (GST-C, SFGT and PG) from baseline to 24 months will be compared. Because of the variable durations of the treatments, we will make a comparison over a time window of 24 months, with assessments taking place at baseline, 3, 6 and 9 months, and at the different end points of the treatments at 12, 18 and 24 months, respectively. Next to the a priori tests over 24 months, we will explore differences between the outcomes of the three treatments on the slopes over time between start of treatment and the respective (different) end points. Differences in outcome at 36 months follow-up will be studied separately. No hypothesis was formulated about the direction of the difference.

The second aim is to study potential mechanisms of change both across therapies and for each specific theoretical framework by determining mediators in repeated measurements during and after therapy, across treatment conditions [58]. Group cohesion, group climate and working alliance are chosen as hypothesized general working mechanisms for group therapy. Another focus of research is the relationship between specific treatment interventions, mediators and outcome. The hypothesis is that certain interventions will be stronger connected to mediators and outcome than others. For example, we expect group dynamic interventions to be positively related to group cohesion.

The third aim is to study potential predictors and its moderating impact on outcome. The hypothesis is that for patients with higher levels of childhood trauma, schema therapy will be more effective, because of its use of trauma-oriented techniques, such as imaginary rescripting [34, 74]. Another hypothesis is that a more structured therapy such as GST-C will yield better results for patients with more severe personality pathology, e.g. borderline personality organization [54]. These patients are less able to tolerate high anxiety levels which can be provoked by the unstructured and exploratory character of PG [39]. Autism traits and vulnerable narcissism will be studied exploratively.

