### Interventions

#### Intervention description {11a}

GST-C is based on the protocol of Farrell and Shaw [30] that has been adapted for the Cluster-C patient [86]. The protocol consists of 30 weekly sessions of 90 min, combined with facultative individual sessions with a maximum of 300 min in total, followed by 4 monthly group booster sessions of 60 min each. Change of schema modes with experiential techniques constitutes the core of the GST-C. The structure of the group is semi-open, with new participants enrolling every 10 sessions, with a maximum of 9 participants in total. The group is led by two therapists, with a third therapist appointed to step in if one of the two therapist is absent. Therapists both have an additional minimum registration of junior schema therapist and are trained in group schema therapy according to Farrell and Shaw [30].

SFGT combines a structured schema-focused approach with an open, unstructured part in one session, thereby giving more room to group dynamics than traditional schema therapy groups [1]. This format is developed to be especially suited for patients with a Cluster-C PD, enabling a focus on intrapersonal and interpersonal dynamics. SFGT consists of three phases, with every 20 sessions new participants enrolling in the group and others terminating. Participants commit to a minimum of 40 sessions, with a maximum of 60. Every session starts with 60 min structured schema therapy interventions, mainly experiential exercises aimed at schema mode change. This is followed by an open group dialogue of 45 min in which group dynamic interventions play a central role using, if appropriate, schema language to interpret and communicate. The group is led by a head therapist and a co-therapist. The head therapist has a minimum registration of junior schema therapist.

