PG makes use of psychodynamic theories and interventions in combination with a focus on the group dynamics [10]. The sessions have an open dialogue character that facilitates a group process in which personality patterns emerge. This enables the therapist to intervene on both the individual level of the patient and on the interaction between patients and the group as a whole. Typical for the psychodynamic framework is to facilitate insight by relating emotions in the here and now to earlier experiences during life [39] and to interpret the transference with the group therapists and the relation with group members as repetitions of earlier relational experiences [10, 62]. In addition, frequently occurring defence and resistance phenomena are discussed to improve the group process, thus making underlying or avoided feelings or fantasies more conscious and beneficial for the patients [10]. PG gives room to spontaneous interactions between group members, facilitating the possibility of interpersonal learning. Through feedback of the group members and group leaders and self-observation, the increase in insight and self-understanding, change in self-image, activation of affects and change of defence style is facilitated. The duration is 80 sessions (2 years) with 90 min sessions. A new participant enrols when another terminates, with a maximum of 9 participants. The group is led by two group therapists, a head therapist and a co-therapist. The minimum qualification for the head therapist is an official specialisation in group therapy. All therapists are trained in a PG protocol that describes the theoretical framework, process and interventions [90], to increase allegiance of therapists and testing adherence.

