#### Provisions for post-trial care {30}

After termination of the treatment, a period of 6 months without psychotherapy is strongly advised. If for any reason additional care is necessary before these 6 months, the patient can reapply for therapy at the NPI, with a referral by the GP. In this case of reapplication, the research committee must be informed and can be involved in the decision making about the following therapy. If the patient reapplies after 6 months, but before the follow-up measurements are conducted, the same procedure is applicable.

No risk of harm is expected by participating in this trial.

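### Adverse events are collected with no stated common enquiry while therapist contact lasts 12, 18 or 24 months by arm, so raw event counts may not be comparable between arms

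*Protocol article*

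**What the plan says.** Adverse event reporting and harms {22} gives the collection method: "Any adverse events reported by the patient or observed by the investigator, other members of the research team or therapists will be documented". The scope is wide: "An adverse event is defined as an undesirable experience that happens to a participant during the study, whether or not related to the experimental intervention". By the abstract's schedule the study runs to 36 months.

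Therapy length differs by design. The abstract lists "group schema therapy for Cluster-C (GST-C, 1 year), schema-focused group therapy (SFGT, 1.5 year) or psychodynamic group therapy (PG, 2 years". Intervention description {11a} gives the contact behind these durations:

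- GST-C: "The protocol consists of 30 weekly sessions of 90 min", "followed by 4 monthly group booster sessions of 60 min each", plus optional individual sessions of up to 300 minutes in all.
- SFGT: 40 to 60 sessions, each with a 60-minute and a 45-minute part.
- PG: "The duration is 80 sessions (2 years) with 90 min sessions".

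On expected harm, Provisions for post-trial care {30} says "No risk of harm is expected by participating in this trial", and section {22} likewise foresees no direct risk. Objectives {7}, explaining why GST-C might suit patients with more severe pathology better, says "These patients are less able to tolerate high anxiety levels which can be provoked by the unstructured and exploratory character of PG". Criteria for discontinuing {11b} lists deterioration of the disorder among the reasons for treatment dropout or push-out.

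**The concern.** One of the named sources of adverse-event information is present for a period set by the randomised arm. Between months 12 and 24 a PG patient still meets two group therapists, while a GST-C patient has finished. Section {30} also strongly advises six months without psychotherapy after treatment ends. If events are noticed less often once therapy is over, the arm observed longest records more events even when true rates are equal, and late events after GST-C or SFGT are under-counted.

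The trial wants to say which therapy suits which patient (end of Objectives {7}). A table of events by arm will be read in that light whether or not it is formally tested. Mean ADP-IV change is not a good substitute: a 1-SD worsening in 10% of one arm moves that arm's mean by 0.10 × 1 = 0.10 SD, against the design difference of d = 0.492 in Sample size {14}.

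**Working it through.** The article gives no adverse-event rate, count or analysis, so there is no stated figure to reproduce. What can be checked is the contact by arm and how far unequal detection could distort counts.

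**Contact by arm (from {11a})**

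- Group sessions: GST-C 30 + 4 = 34; SFGT 40-60; PG 80.
- PG/GST-C = 80/34 = 2.35. SFGT/GST-C = 40/34 to 60/34 = 1.18 to 1.76.
- In minutes, with the maximum individual time counted for GST-C: 30×90 + 4×60 + 300 = 3,240. PG: 80×90 = 7,200. Ratio 7,200/3,240 = 2.22.

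**Recorded events under equal true rates**

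Let T be therapy months (12, 18, 24), H the window (24 or 36 months), p_in the detection probability during therapy and p_out that afterwards. Recorded events are proportional to p_in×T + p_out×(H − T). The true rate cancels in the ratio between arms. The article gives neither probability, so both are assumptions. Full-length therapy is also assumed.

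Worked case, p_in = 0.8 and p_out = 0.3:

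- 24 months: GST-C 0.8×12 + 0.3×12 = 13.2; SFGT 0.8×18 + 0.3×6 = 16.2; PG 0.8×24 = 19.2. PG/GST-C = 19.2/13.2 = 1.45; SFGT/GST-C = 16.2/13.2 = 1.23.
- 36 months: GST-C 0.8×12 + 0.3×24 = 16.8; SFGT 0.8×18 + 0.3×18 = 19.8; PG 0.8×24 + 0.3×12 = 22.8. PG/GST-C = 22.8/16.8 = 1.36; SFGT/GST-C = 19.8/16.8 = 1.18.

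Only k = p_out/p_in matters. For PG/GST-C the ratio is 2/(1 + k) over 24 months and (2 + k)/(1 + 2k) over 36 months.

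| p_in, p_out | PG/GST-C, 24 months | PG/GST-C, 36 months |
|---|---|---|
| 0.8, 0 | 2.00 | 2.00 |
| 0.8, 0.1 | 1.78 | 1.70 |
| 0.8, 0.3 | 1.45 | 1.36 |
| 0.8, 0.5 | 1.23 | 1.17 |
| 0.8, 0.8 | 1.00 | 1.00 |

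The distortion therefore runs from none to a doubling. A common enquiry at common time-points aims at the last row, where the expected ratio is 1.00.

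**The case against.** The strongest reply has four parts.

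1. **The article is a condensed text.** It does not say whether patients are asked about events, and the full protocol may contain a solicited procedure. This stands, and it limits the point to the method as described.

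2. **Therapists are only one source, and the detection rates are assumed.** A reader might infer that most reports come from therapists, that counts will differ by arm, or that PG will look less safe. The article supports none of these. Section {22} names patients, investigator and research team too, without weighting, and equal detection gives a ratio of 1.00. Counts may differ; no more can be said.

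3. **Worsening is captured by routes that do not depend on the arm.** The assessment schedule is stated without distinction by arm to 36 months, and the outcomes include the ADP-IV and BSI. Secondary study parameters lists reliable change. The TiC-P FORCE asks about health care contacts in the last six months. Section {30} requires the research committee to be told when a patient reapplies for care. Section {18b} has researchers contact patients to complete follow-up. So it would be wrong to infer that the trial could not say who worsens. Yet none of these is a common adverse-event enquiry. The dropout questionnaire in Treatment retention does not fill the gap, because the therapist completes it when treatment is discontinued.

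4. **No between-arm comparison of events is planned.** True, so no stated analysis is biased. The caution concerns how documented events will be tabulated and read.

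A reader might also infer that the protocol predicts a harm of PG and then fails to measure it. It does not. The anxiety remark in {7} is the rationale for a moderator hypothesis, and that hypothesis has an analysis on the ADP-IV under Differential treatment response. The no-risk statements can also be read as concerning trial participation rather than the therapies. What remains is a tension in wording.

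**Conclusion.** The point holds as a risk of unequal ascertainment. As described, event recording has no stated common enquiry, covers the whole study, and relies in part on therapists whose contact lasts 12, 18 or 24 months by arm. Raw counts would not be safely comparable between arms.

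The size is not derivable from the article. Under equal true rates and full-length therapy, the recorded PG/GST-C ratio over 24 months lies between 1.00 and 2.00 as long as detection after therapy is no better than during it. The value 1.45 is an illustration at assumed detection of 80% and 30%. Severity is low to moderate: no planned analysis is invalidated, other outcomes partly capture worsening, and the full protocol may already provide a solicited procedure. The remedy is cheap enough to be worth making.

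**What to change.** 1. Add the same short adverse-event questions (for example worsening, suicidality, hospital admission, new crisis care), covering the time since the previous assessment, to the existing online survey at the common assessment points to 36 months in all arms. If the full protocol already does this, say so in section {22}.

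2. Base any between-arm harm summary on these solicited events over common windows, 0-24 and 0-36 months. List therapist-observed events separately. For the 167 patients already included at submission, start the window at the amendment or ask about earlier events retrospectively.

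3. Within the reliable-change outcome already listed, report the proportion per arm with reliable worsening on the ADP-IV and BSI, including by baseline IPO-83 level. This uses scores already collected.

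4. Reconcile the statements in {30} and {22} that no risk is expected with the anxiety that {7} attributes to PG and the deterioration listed in {11b}. This is a matter of wording and changes no result.

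The cost is a few survey items, slight patient burden, more events recorded and one amendment.

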### Frequency and plans for auditing trial conduct {23}

At the moment, no audit is planned for trial conduct.

### Plans for communicating important protocol amendments to relevant parties (e.g. trial participants, ethical committees) {25}

Important protocol amendments will be proposed to the ethical committee of the VU Amsterdam and if applicable, with the therapists and the research participants.

### Dissemination plans {31a}

We will submit the trial results to a peer-reviewed journal. The final article will be shared with all the participants and therapists of the study.

## Discussion

This randomized controlled trial aims to bridge the gap between actual clinical practice that offers different types of group therapy for Cluster-C PDs and the almost absence of an evidence base. This scientific neglect in the study of Cluster-C PDs makes it practically impossible to inform patients reliably about valuable treatment options. Considering the high frequency of Cluster-C PDs and its negative impact on quality of life and the effectiveness of treatments for other common mental health disorders, there is clearly an urgent need to ameliorate this state of affairs.

With individual therapy as the focus of previous research [9, 83], G-FORCE will be the first RCT on group therapy for Cluster-C PDs. Group therapy has many advantages, such as the possibility of interpersonal learning. Also, several meta‐analyses have found no difference between effectiveness of group and individual therapy for several theoretical orientations and across various disorders, such as anxiety and mood disorders [17, 76].

G-FORCE is designed to investigate the differential effectiveness of two forms of schema group therapy (GST-C and SFGT) and psychodynamic group therapy for Cluster-C PDs and to study the general and theory-specific predictors and working mechanisms. In this study, patients are not only included with a specific Cluster-C PD but also with a diagnosis of an otherwise specified PD with Cluster-C traits and with a wide range of psychiatric comorbidity.

### Strengths

To our best knowledge, this study is the first to compare directly two important theoretical frameworks of group therapy: schema group psychotherapy and psychodynamic group psychotherapy. Regarding schema group therapy, controlled studies do exist [31, 100], but all were focused on borderline PD (BPD). With the development of a group schema therapy for Cluster-C patients (GST-C), the first promising results of a pilot study on its effectiveness, and a currently running RCT comparing GST-C with individual schema therapy [7, 43], the evidence for schema therapy for this type of patients is starting to grow. G-FORCE contributes to this line of research, with a unique comparison between two forms of schema group therapy and psychodynamic group therapy.

Another distinctive feature of the study is that the three forms of group therapy are dimensionally distributed on a spectrum, with structured, short duration GST-C on the one end, unstructured and long duration PG on the other end, and SFGT in the middle, representing a combination of structured group schema therapy and unstructured dynamic group therapy.

In the field of PG, evidence is mainly coming from open cohorts and mixed diagnostic groups. This shortcoming of evidence also reflects a lack of uniformed and sufficiently transparent manuals on psychodynamic or psycho-analytic group therapy [76]. By designing the G-FORCE study, a protocol was developed for PG, meeting the need for more transparency that is asked by patients and other stakeholders.

The only controlled study on the effectiveness for PDs compared short-term with long-term psychoanalytic group therapy [63]. With our study, PG will be compared with schema therapy, thus broadening the evidence to the differential effectiveness of group therapy approaches stemming from distinctive theoretical frameworks.

Another important strength of this trial is its pragmatic character. In pragmatic trials, the interventions in real-life routine practice settings are researched [34]. This means the findings are highly generalizable and potentially beneficial for clinical practice [71]. The majority of the participants of this study received individual treatment before and will receive group therapy for the first time.

Finally, the design of the current study enables us to investigate both the predictors and treatment processes during group therapy. Treatment interventions, potential mediators and outcome are measured repeatedly during treatment, meeting the condition of establishing a temporal relationship between the variables. In this way, we aim to contribute to answer the question which treatment works for whom and why.

### Limitations

Some limitations must be considered. First, we are not able to compare any of the treatments with a ‘golden standard’. Also, no comparison will be made with a non-active control-group as this is perceived unethical in view of the long waiting lists for the participating departments and the long duration of the therapies. Moreover, all the interventions in this study could possibly be considered as the treatment as usual (TAU) in Dutch clinical practice or as experimental interventions that have yet to be established. Compared to PG, GST-C is more recently developed and based on a clearly defined protocol. For SFGT, a protocol had been published internally, based on publication of Aalders & van Dijk [1]. PG has, by nature, a more open structure and more differences in how it is applied in clinical practice. That is why we have developed a manual for the psychodynamic group with experts in the field ([name], [name], [name] & [name], 2021, internal publication), enabling this therapy to be delivered in a transparent and uniform way. A more general description has been published recently as well [84]. This protocol enables us to assess adherence and competence also of PG. We therefore consider none of the applied therapy forms as a condition that would represent TAU. In addition, all therapies are offered in a highly specialized institute for PD. This implies an ongoing context of peer—and expert supervision and quality evaluations that are normally not available in context of TAU, while the main therapists are all highly qualified, with broad experience in PG.

In the current study, no comparison is made between group therapy and individual therapy. Although this would be valuable, we expected a negative impact of randomisation between individual and group therapy, such as increased dropout rates and difficulties with motivation and enrolment of patients. Therefore, a separate RCT on individual therapy for cluster C pathology (I-FORCE) has been developed and is currently running (Daniëls et al. in prep.).

Another limitation is the different duration of the treatment modalities. Although we ruled out the confounding effect of time by setting the end point of the main outcome measurements at 24 months, it will not be clear what the confounding effect of dosage could be. Difference in dosage is due to the pragmatic character of the study in researching existing group therapy formats, with varying duration and dosage. Because of these different dosages, determining cost-effectiveness at follow-up is of extra importance in this study. However, the difference in dosage and amount of structure in the compared therapies gives, in combination with the extensive study of predictors and potential moderators, the opportunity to gain valuable knowledge about which therapy is best for which type of Cluster C patient, hereby optimizing the possibility of matched or personalized care.

To conclude, in the sample size calculation, we did not adjust for dropout, which could negatively affect the power. Nevertheless, mixed regression with multiple measurements over 2 years is expected to balance out this potential loss of power because of the particular strength of this type of analysis.

As far as we know, G-FORCE will be the first large pragmatic RCT on the effectiveness of group therapy for Cluster-C PDs, contributing to growing evidence on effective Cluster-C treatments and group psychotherapy. With its focus on possible predictors and mediators, G-FORCE will increase our understanding on which therapy works for whom and why, helping to recommend the best available clinical treatment for the individual patient with a Cluster-C PD diagnosis.

